## Outcome measurements

### Primary outcome

#### Weight and body mass index (BMI)

The primary focus of the outcome measurements is on the effectiveness of the interventions in reducing the severity of overweight or obesity. It includes the change in body weight in Kg and BMI. BMI is a commonly used tool for assessing the risk of overweight and obesity for individuals [1]. It is calculated using the following equation:$$\mathrm{BMI}=\frac{\mathrm{Mass}\ \left(\mathrm{Kg}\right)}{\left(\mathrm{Height}\ \left(\mathrm{m}\right)\right){\mathrm{H}}^2}$$

#### Waist and hip ratio (WHR)

WHR is another commonly used tool to measure central obesity, which will be calculated as:$$\mathrm{WHR}=\frac{\mathrm{Waist}\kern0.5em \mathrm{circumference}\kern0.5em \left(\mathrm{cm}\right)}{\mathrm{Hip}\kern0.5em \mathrm{circumference}\kern0.5em \left(\mathrm{cm}\right)}$$

Participants will be required to wear similar types of clothing to avoid the influence of clothing on the measured weight and the circumferences.

#### Body composition

Body composition involves measuring the body fat percentage (Fat %) by using the Dual Energy X-ray Absorptiometry (DXA) scan. DXA is a type of medical imaging technology which uses low dose radiation for the whole-body scan to provide the measurement of Fat %. The scanning will be performed by qualified operators.

The measurements of body composition will be taken from the baseline, the 12th and 20th-week visit.

### Secondary outcomes

#### Weight-Related Symptom Measure (WRSM) and Obesity and Weight Loss Quality of Life (OWL-QOL)

WRSM and OWL-QOL are two qualitative instruments to evaluate the weight-related quality of life and symptoms. WRSM is a 20-item questionnaire that evaluates the weight-related symptoms such as tiredness and increased appetite. The responses will be recorded on a 0 to 6 points scale, where 0 indicates not at all and 6 indicate a very great deal. The higher the total score indicates more weight-related symptoms which affect the ‘participants’ well-being. The OWL-QOL is a 17-item questionnaire that measures ‘participants’ weight-related feelings. Participants will respond to questions similar to ‘Because of my weight, I try to wear clothes that hide my shape’ or ‘I feel ugly because of my weight’. The responses will be recorded on a 0–6-point scale, where 0 indicates not at all and 6 indicate a very great deal. The higher the total score indicates the quality of life is being affected by obesity.

#### Power of Food Scale

Power of Food Scale (PSF) is a 15-item scale which measures psychological influence on food intake, particularly in an environment where palatable food is highly abundant. Participants will respond to questions like ‘I think I enjoy food more than many other people or I cannot help myself thinking about food’. The responses will be recorded in a 1- to 5-point scale, where 1 indicates disagree and 5 indicates strongly agree. The higher the total score indicates a higher food intake due to psychological influence.

#### Frequency of practising MM

The self-practice MM will also be recorded to assess the correlation between the frequencies of practice with other measured outcomes. A log book will be given to participants who are allocated to EAM and SAM groups. Participants will have an option to submit a photo of their log book via email or to hand in the hard copy.

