### Exclusion criteria

Participants will be excluded if they have one or more of the following conditions:Serious chronic medical conditions, such as cardiovascular diseases, cancer, HIV, and epilepsy;Women who are pregnant or lactating;Drug-induced secondary obesity;Medical conditions which are known to link with obesity, such as uncontrolled high blood pressure, polycystic ovary syndrome, hypothyroidism, Cushing syndrome, and Hashimoto’s disease;Mental conditions such as clinical depression, anxiety, PTSD, and psychosis;Participants who are not willing to be treated by acupuncture or to practice meditation;Difficulties with understanding and reading English;Taking blood-thinning medications;Auditory impairment who cannot listen to audio records; andParticipants who received treatment for obesity in the past 3 months, including medical treatment or participated in weight loss programs.

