### Group design

This is a three-arm clinical trial, which consists of the EA plus MM group (EAM), SEA plus MM group (SAM) and EA only group (EAO). Participants will be asked to continue with their usual diet and exercise, and refrain from participating in any weight loss program or consuming any weight loss supplements/medications, otherwise will be considered as a dropout during the study. The description of each group is listed below (Table 2):

**Table 2 Tab2:** Group description

Group	Description
Electroacupuncture + MM (EAM)	This group consists of a combination of EA and mindfulness meditation interventions. Participants will be given the abovementioned EA treatment. They will then be prompted to follow the 10 min pre-recorded MM instruction. They will be instructed to practice MM daily.
Sham electroacupuncture + MM (SAM)	This group consists of a combination of EA and mindfulness meditation interventions. Participants will be given the abovementioned sham EA treatment. They will then be prompted to follow the 10 min pre-recorded MM instruction. They will be instructed to practice MM daily.
Electroacupuncture only (EAO)	This group consists of the abovementioned electroacupuncture treatment only.

*Abbreviations*: *MM* Mindfulness meditation, *EA* Electro-acupuncture

The add-on effect of MM to EA comparing the treatment group (EAM) with the control group (SAM). On the other hand, to assess the add-on effect of electroacupuncture on mindfulness meditation, the treatment group (EAM) will be compared with the control group (EAO).

Participants will confirm their next appointment during their visits, and a message will be sent to the participants to remind and confirm their weekly visits.

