## Discussion

Overweight and obesity have reached an epidemic level across the world over the past decades [1]. More effective weight management strategies are urgently needed to reduce the prevalence and impacts on our society. Due to the multifactorial cause of overweight and obesity, interventions that only target one single factor may not achieve a satisfying weight management outcome [60–62].

Evidence has shown that acupuncture is effective in weight management when it is being used alone or combined with other weight loss interviews to enhance weight loss outcomes [32, 38, 40]. EA is a variant of acupuncture with a replicable mode of stimulation that enables consistent stimulation throughout treatment sessions [21]. Additionally, other evidence has suggested that mindfulness meditation may be added to weight loss programs to enhance the treatment results [52]. Furthermore, the clinical practice guidelines for the management of overweight and obesity in adults, adolescents and children in Australia suggest that psychological component can be added to weight loss programs to increase the likelihood of success [11]. To our best knowledge, this is the first trial protocol evaluating the effect and safety of EA combined with mindfulness meditation for weight management.

The aim of this RCT is to evaluate the add-on effect of EA and MM on weight loss. In terms of group design, the add-on effect of EA will be evaluated by comparing the EAM group and SAM group. The add-on effect of MM will be assessed by comparing the EAM group and the EAO group. This design has put a limitation on this trial in which we cannot blind the participants for the EAO group who will not be participating in the MM component. Participants in the EAM and SAM groups will be blinded by sham electroacupuncture treatment. The SA method was designed as penetrating insertion to a non-acupuncture point, all acupuncturists will receive training on needling to the predefined non-acupuncture points to ensure consistency of point location for the SAM group. The wire of the electro-stimulator will be modified to stop the current being flow to the body; this ensures that the SAM group participants receive no electro-stimulations at all. Participants will be told that the intensity of stimulation is predefined, and therefore they may or may not be able to feel for the stimulation.

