Participants in EAM and SAM groups are required to practice MM daily and record their practice in a log book. The pre-recorded MM instructions will increase the flexibility for participants to practice MM at their preferable time.

Both objective and subjective outcome measurements will be evaluated in this trial. The current management of overweight and obesity includes lifestyle changes, pharmacotherapies and surgeries [63], and it is necessary to isolate the effect of these approaches to impact the study results. Therefore, participants will be asked not to undergo bariatric surgery or consume weight loss medications and continue their usual diet and physical activities. As a result, we can ensure that the change in the treatment outcome was attributed to the effect of the allocation study group. Although BMI is the major tool for assessing weight status [1], body fat composition will also be evaluated because it is necessary to investigate whether the reduction in BMI is due to the loss of body fat, muscle mass or bone density [64, 65]. Moreover, WHR is a commonly used tool for assessing abdominal obesity, linked closely to cardiovascular disease risk [66]. The idea of addressing overweight and obesity is to reduce the risk for other comorbidities like cardiovascular diseases [67]. Therefore, WHR will also be assessed to evaluate the effect of this combined intervention on abdominal obesity [68].

The WRSM, OWL-QoL, and Power of Food Scale were used to assess the psychological impact on overweight and obesity [69, 70]. If the result of this RCT is found positive, it will provide a novel cost-effect multicomponent weight management approach. It is anticipated that this approach may improve both physical and psychological outcomes for overweight and obese individuals.

Finally, this rigorously designed clinical trial protocol was developed by following the SPIRIT [54], CONSORT [56], and STRICTA [55] guidelines to minimize the risk of bias and the quality assurance for the combined intervention. If successful, this proposed protocol may provide a safe and cost-effective multidisciplinary approach for weight management.

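### Meditation is recorded only in the two meditation arms and not restricted in the electroacupuncture-only arm, so practice there could dilute the mindfulness contrast unseen

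*Protocol article*

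**What the plan says.** All references are to the Protocol article.

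- **Who is logged.** Section *Frequency of practising MM*: "A log book will be given to participants who are allocated to EAM and SAM groups". The *Discussion* repeats this: "Participants in EAM and SAM groups are required to practice MM daily and record their practice in a log book".
- **What the log is for.** The same section gives its purpose: "The self-practice MM will also be recorded to assess the correlation between the frequencies of practice with other measured outcomes". That is a dose-response use within the meditation arms, not a check on the control arm.
- **What participants must avoid.** *Group design*: "Participants will be asked to continue with their usual diet and exercise, and refrain from participating in any weight loss program", with supplements and medications added in the same sentence. *Attendance and drop-out* adds bariatric surgery. Neither names meditation.
- **What EAO receives.** Table 2 in *Group design*: "This group consists of the abovementioned electroacupuncture treatment only". No instruction about meditating is given.
- **Blinding.** *Discussion*: "we cannot blind the participants for the EAO group who will not be participating in the MM component".
- **Entry.** The one criterion on meditation, in *Exclusion criteria*, removes this group: "Participants who are not willing to be treated by acupuncture or to practice meditation".
- **Which contrast tests meditation.** The *Discussion* assigns the add-on effect of meditation to EAM versus EAO. *Group design* assigns it to EAM versus SAM, with the two contrasts the other way round. The arms' contents support the *Discussion*, but the two sections must be reconciled.

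**The concern.** EAM minus EAO estimates what meditation adds to electroacupuncture over an untreated background only to the extent that EAO participants do not meditate. Everyone randomised has declared a willingness to meditate. Those allocated to EAO know which component they lack, and much of the assigned meditation is a ten-minute daily home practice that needs no equipment. Some of them may meditate on their own initiative over the 20 weeks after baseline.

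If they do, the difference shrinks, and the data described would not show why. A null result could mean that meditation adds nothing, or that part of the control arm also meditated. The *Discussion* says that the restrictions on other weight-loss approaches allow a change in outcome to be attributed to the allocated group. For this contrast that assurance is not supported, because the restrictions omit the one factor that separates the two arms.

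**Working it through.** **1. Is practice in EAO recorded anywhere?** The log goes to EAM and SAM. The other listed secondary measures are the WRSM (weight-related symptoms), the OWL-QOL (weight-related feelings), the Power of Food Scale (psychological influence of food) and the Chinese medicine questionnaire (symptom patterns). As described, none asks about meditation. A screening questionnaire is mentioned in *Recruitment and screening*. Its items are not shown, and it is completed before randomisation, so it could capture prior practice but not practice during the trial.

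**2. Is practice in EAO restricted?** Joining a weight-loss programme is, so mindfulness delivered within such a programme is covered. General or self-guided meditation is not.

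**3. The plan's own sample-size figure.** Inputs from *Sample size*: effect 0.56 SD (acupuncture versus sham, on BMI), 80% power, 5% significance, 55 per group. *Statistical analysis* makes tests two-sided.

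- Normal approximation: n = 2(1.96 + 0.8416)² / 0.56² = 15.70 / 0.3136 = 50.1, so 51 per group.
- Exact t calculation: 52 per group.

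The stated 55 is not matched exactly, but it is on the safe side: it would follow from 52 / 0.95 = 54.7 if 5% dropout had been allowed for, which the article does not say. This point does not depend on the gap.

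**4. Illustration of dilution.** Let p be the share of EAO who meditate and b the fraction of the meditation benefit that they obtain. The expected contrast is d(1 − pb). Write c = pb for the net dilution. The article gives neither p nor b, nor d for meditation. Here d = 0.56 is borrowed and c is assumed.

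Normal approximation: power = Φ(d(1 − c)√(n/2) − 1.96), with √(55/2) = 5.244. At c = 0 this is Φ(2.937 − 1.96) = Φ(0.977) = 83.6%.

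| Net dilution c (assumed) | Contrast (SD) | Power, normal | Power, t-test | n per group for 80% (t-test) |
|---|---|---|---|---|
| 0 | 0.560 | 83.6% | 82.9% | 52 |
| 5% | 0.532 | 79.7% | 79.0% | 57 |
| 10% | 0.504 | 75.3% | 74.5% | 63 |
| 20% | 0.448 | 65.1% | 64.4% | 80 |
| 30% | 0.392 | 53.8% | 53.1% | 104 |

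c is not the same as the share who meditate. If 20% of EAO meditate and gain half the benefit, c = 0.20 × 0.5 = 10%. These are simple two-sample figures. The planned ANCOVA could raise the level of power, but it would not remove the dilution.

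**The case against.** **A practice log for the arms assigned to practise is ordinary, and a condensed article may leave the rest elsewhere.** Part of this stands. Prior practice may be asked about in the screening questionnaire, and the consent form or other trial papers may instruct EAO participants. So the documents do not show that contamination could never be detected or that nothing at all restrains EAO. They show only that no in-trial measure and no restriction is described. That is still more than silence, because the article itself states who gets the log and lists what participants must avoid.

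**The trial's recording and booklet are described only for the meditation arms.** This stands. Contamination would mean self-initiated practice, which need not match a prompted daily programme. Full benefit for EAO meditators is therefore an upper bound.

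**Randomisation balances prior meditators.** This stands. A reader might infer from the entry rules that admitting regular meditators biases the comparison and that they should be excluded. The documents do not support that. The willingness criterion applies to all arms and is needed before allocation, prior practice is balanced in expectation, and its effect is dilution. Excluding meditators would also narrow the population, which is a debatable trade.

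**The contrast remains a valid estimate of adding the meditation prescription to usual behaviour, and dilution is conservative for a superiority claim.** This is true of a positive result. It does not help in reading a null one.

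**Conclusion.** The concern holds as a limit on interpretation. Practice in the unblinded comparator arm is neither recorded nor restricted in anything the article describes, so a null EAM-EAO result could not be attributed with confidence.

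The size cannot be known from the document. A reader might infer from the power table that the trial is underpowered for the meditation question. That does not follow: 0.56 SD is an acupuncture-versus-sham effect, and the 10% to 30% dilutions have no source in the article. The figures show sensitivity only. On those assumptions a net loss of about 5% takes power just below 80%, and 10%, 20% or 30% takes it to about 75%, 64% or 53%. The mechanism does not depend on these inputs. This is a cheap improvement to the design; it does not show that the comparison is invalid.

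**What to change.** 1. In *Frequency of practising MM*, ask all three arms one brief question on meditation practice since the last visit, at the assessment visits already planned (weeks 3, 6, 9, 12, 14, 16 and 20). Keep the daily log for EAM and SAM only.
2. Record prior meditation practice at baseline, if the screening questionnaire does not already do so, and use it as a covariate in the EAM-EAO comparison.
3. In *Group design*, add a sentence asking EAO participants not to start a new meditation practice until the week-20 visit. Do not exclude current meditators.
4. Reconcile *Group design* with the *Discussion* on which contrast tests which component.

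The cost is one short question at existing visits, at most one baseline item, and small text changes. Eligibility is unchanged. Recruitment was in progress when the article appeared, so the question can start with current participants, but earlier visits will lack it. The one real downside is that repeated asking could slightly prompt practice in EAO, so the question should be worded neutrally.

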#### Chinese medicine differential diagnosis questionnaire

The Chinese medicine differential diagnosis questionnaire will be used during the baseline measurement. The questionnaire will differentiate participants' symptoms into 5 different patterns according to Chinese medicine theory. The patterns will be used for data analysis on whether EA for weight management is in favour of any type of Chinese medicine differential pattern.

Except for body composition, the abovementioned outcome measurements will be assessed at the endpoints of 3, 6, 9, 12, 14,16, and 20th week.

### Adverse events

All adverse events will be documented, including the description, severity, duration, and the required treatment. All cases of serious adverse events will be immediately reported to the chief investigator for appropriate action. All severe adverse events will be reported to RMIT Human Research Ethics Committee (HREC), and the RMIT HREC will make the final decision on the termination of the trial.

### Attendance and drop-out

Participants will be informed that they are free to withdraw from the clinical trials at any time. The attendance to the treatment will be recorded for participant adherence. The reason for withdrawal will also be followed up and documented. Participants are not obligated to provide a reason for withdrawal. However, if the reason is related to adverse events, they will be follow-up until the issue is completely resolved. Participants who undergo bariatric surgery, consume weight loss medication, or participate in another weight loss program during this study will be considered drop-out.

### Data management

The personal information and records of each participant will be kept in an individual file and stored in a locked cabinet. All electronic documents will be stored in an RMIT University computer with password protection. Access to all research data will only be permitted to an authorized research team member.

All participants will receive a summary of study findings and group information upon trial completion. All personal identities will be removed before the publication of the trial findings.

### Statistical analysis

Statistical analysis will be performed using Statistical Package for Social Science (SPSS) at the Discipline of Chinese Medicine, School of Health and Biomedical Science, RMIT University, at the end of the trial. Given the short duration of the trial, no interim analysis will be conducted. Intention-to-treat (ITT) analysis will be used for participants who are randomized and participated for at least one treatment session. The Worst-Case Scenario method will be employed to deal with the missing data. Continuous variables will be summarised using the mean, standard deviation, and 95% confidence intervals, while quantitative variables will be presented using the maximum and minimum values. Baseline data and clinical characteristics will be used to compare the baseline data between intervention groups. Analysis of covariance (ANCOVA) will be performed on BMI and WHR to determine the mean difference between groups at the end of treatment and follow-up period. All comparisons will be two-tailed, and *p* values < 0.05 will be considered statistically significant.

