### Sample size

The sample size was calculated based on a previous study comparing the acupuncture group with the sham acupuncture for BMI [57]. After the treatment, the effect size estimate was 0.56. The sample required to achieve 80 per cent power at a significance level of 5% is 55 per group (total *n* = 165).

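### An undefined worst-case imputation is the only missing-data rule for the ANCOVA of BMI and WHR; depending on its reading it attenuates the effect, costs power or inflates type I error

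*Protocol article*

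**What the plan says.** All of the following is in the protocol article.

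- **Missing data (Statistical analysis):** "The Worst-Case Scenario method will be employed to deal with the missing data". The rule is not defined, not limited to particular outcomes and not labelled a sensitivity analysis.
- **Analysis set (same section):** "Intention-to-treat (ITT) analysis will be used for participants who are randomized and participated for at least one treatment session". People without endpoint data therefore stay in and need a value.
- **Main analysis (same section):** ANCOVA "will be performed on BMI and WHR to determine the mean difference between groups at the end of treatment and follow-up period".
- **Sample size:** an effect of 0.56 on BMI is taken from a previous study, and the conclusion drawn from it reads "The sample required to achieve 80 per cent power at a significance level of 5% is 55 per group". No dropout allowance is mentioned.
- **Visits (end of Secondary outcomes):** body composition apart, "the abovementioned outcome measurements will be assessed at the endpoints of 3, 6, 9, 12", then 14, 16 and 20 weeks. The Body composition section gives DXA at baseline, week 12 and week 20 only.
- **Dropout:** the Attendance and drop-out section counts anyone who starts another weight-loss treatment as a drop-out. The Discussion concedes that "we cannot blind the participants for the EAO group". The Group design table gives daily meditation to EAM and SAM only.

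**The concern.** BMI and WHR have no natural worst value. Whoever runs the analysis has to choose one, and the choice can drive the result. An extreme value put in for each missing one pulls an arm's mean in proportion to its dropout, widens the variance, and is then analysed as if it had been observed. If dropout is equal, a real effect may be missed. If it is unequal, a difference can appear where there is none, against whichever arm loses more people. The article states this rule outright, so a conforming analysis plan would inherit it. Meanwhile the visit schedule offers earlier BMI and WHR values for many people who miss an endpoint, and a better-founded method could use them.

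**Working it through.** **Inputs from the article:** 55 per group, standardized difference 0.56, 5% significance, "All comparisons will be two-tailed".

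**Assumptions, because the article gives no figures:** dropout rates as shown below; dropout completely at random; change in BMI Normal with SD 1; one pairwise comparison.

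**1. The plan's own figure.** n = 2(1.960 + 0.842)² / 0.56² = 2 × 7.85 / 0.3136 = 50.1, so 51 per group (52 with the t distribution). The stated 55 does not reproduce exactly but errs on the large side. Power at 55 is 83.6% (normal) or 82.9% (t). Nothing below depends on this gap.

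**2. Worst observed change given to every missing participant.** Let m be that value, p_T and p_C the dropout proportions, and μ_T and μ_C the true mean changes.

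Estimated difference = (1 − p_T)μ_T − (1 − p_C)μ_C + (p_T − p_C)m.

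- *No true effect, 10% against 20%:* about 94 of 110 values are observed and m averages about 2.48 SD. Bias = 0.10 × 2.48 = 0.25 SD against the arm with more dropout. Simulated type I error is about 17%.
- *True effect 0.56, equal dropout p:* estimate = (1 − p) × 0.56, which is 0.53 at 5%, 0.50 at 10%, 0.48 at 15% and 0.45 at 20%.
- *Power at 15%:* variance per arm = (1 − p) + p(1 − p)(m − μ)². With m about 2.29, control is 0.85 + 0.1275 × 2.29² = 1.52 and treatment is 0.85 + 0.1275 × 2.85² = 1.89. SE = √((1.52 + 1.89)/55) = 0.249. z = 0.476/0.249 = 1.91. Power ≈ Φ(1.91 − 1.96) = 48%. Simulation gives 48%, against 76-77% for complete cases. At 5% dropout it gives 68%.

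**3. Worst change within the participant's own arm.** The arm's maximum is a random quantity copied to all its dropouts, but the test counts the copies as independent observations. Simulated type I error is about 9% at 15% equal dropout and 11% at 20%.

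**4. Milder readings.**

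| Reading | Estimate (true 0.56) | Power | Type I error |
|---|---|---|---|
| Participant's own worst value, 10% / 20% / 30% equal dropout | 0.51 / 0.46 / 0.41 | 0.75 / 0.68 / 0.62 | 0.05-0.06; 0.06 at 10% v 20%; 0.12 at 10% v 30% |
| No change from baseline, 15% equal dropout | 0.85 × 0.56 = 0.48 | about 0.76 | 0.05, also at 10% v 20% |
| Completers only, for reference, 10% / 20% / 30% | 0.56 | 0.78 / 0.74 / 0.66 | about 0.05 |

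The no-change row assumes that controls do not change on average. At 20% dropout that reading gives 0.80 × 0.56 = 0.45. The other two rows come from a simulated week-12 ANCOVA (assumed baseline BMI SD 3.5, last attended visit uniform over baseline and weeks 3, 6 and 9).

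**5. Alternative.** A likelihood repeated-measures model on weeks 3, 6, 9 and 12 gave estimates of 0.55-0.56. Power was 0.78 / 0.77 / 0.74 at 10 / 20 / 30% equal dropout, and type I error 0.04-0.05, including at 10% v 20% and 10% v 30%. The covariance was treated as known (assumed correlation of week-9 and week-12 change 0.76), which flatters it slightly.

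**6. What earlier data exist.** Someone missing week 12 has at most three earlier post-baseline values of BMI and WHR (weeks 3, 6, 9). An early dropout may have none. Body fat % has none before week 12.

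**The case against.** The strongest defence is that the rule is undefined and may be meant mildly. Under the mild readings power stays near that of completers and type I error near 5% unless dropout is very unequal. That stands, and it limits what can be claimed. Four stronger readings are tempting.

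- **That every version of worst case wrecks the result.** The documents do not support this: mild versions mainly attenuate, and low dropout does less harm.
- **That the trial's effect would be reversed.** A reader might infer this from imputing the worst for EAM and the best for its control. Nothing in the article points to opposite imputation by arm.
- **That the bias favours EAM.** EAO is unblinded, so it may lose more people. But EAM carries daily practice and a log book that EAO does not, and the Discussion describes EAM and SAM as blinded. Dropout may be unequal in either direction.
- **That seven collected measurements are thrown away.** Seven is the number of scheduled post-baseline visits, and the Trial status section says recruitment was still in progress. At most three precede week 12, and the own-worst-value reading does use earlier visits.

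It is also fair to say that a repeated-measures model assumes missing at random. That is doubtful here, since starting other weight-loss treatment counts as dropout. The simulations used completely random dropout and do not test the model under that pattern. This argues for sensitivity analyses; it does not rescue an undefined main rule.

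**Conclusion.** The point holds in a conditional form. The article fixes one undefined worst-case rule as the only handling of missing data in the main ANCOVA, and the consequence depends on how the rule is read.

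- **Worst observed value for all:** a severe loss of power at 15% equal dropout (to about 48%), and about 17% type I error at 10% v 20%.
- **Worst within arm:** 9-11% type I error at 15-20% equal dropout.
- **Mild readings:** chiefly attenuation, to about 0.45-0.51 at 10-20% dropout.

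These sizes rest on assumed dropout rates, completely random dropout and Normal changes with SD 1; the article supplies none of these. Because completers alone give an unbiased estimate in that setting, the distortion comes from the imputation itself. It is not reliably conservative either, since it can create an apparent benefit when a control arm loses more people.

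**What to change.** In the Statistical analysis section, replace the missing-data sentence along these lines: *BMI and WHR will be analysed with a likelihood-based repeated-measures model using all attended post-baseline visits, with baseline value, arm, week and arm-by-week interaction; arm contrasts will be reported at weeks 12 and 20.* Multiple imputation from the same visits would also serve.

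Keep two labelled sensitivity analyses:

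- a worst-case analysis that states which value is imputed, from whom it is taken, and whether it is on the change or the absolute scale;
- a delta-adjusted (tipping-point) analysis.

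For body fat %, acknowledge that no earlier post-baseline value exists before week 12.

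The cost is wording and modest programming with a mixed-model procedure in SPSS; no new data are needed. The article plans no interim analysis and reports recruitment in progress, so the change could be dated before any unblinded analysis. The drawback is reliance on missing at random, which the two sensitivity analyses are there to probe.
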